## SYNOPSIS

|                                                   |                                                                                                                                                                                                                                                                                                                                                                                                                                                                                                                                                                                                                                                                          |
|---------------------------------------------------|--------------------------------------------------------------------------------------------------------------------------------------------------------------------------------------------------------------------------------------------------------------------------------------------------------------------------------------------------------------------------------------------------------------------------------------------------------------------------------------------------------------------------------------------------------------------------------------------------------------------------------------------------------------------------|
| HYPOTHESIS                                 | 
To evaluate whether the intervention group has a larger improvement in the healthy lifestyle questionnaire score than the comparison group, the following hypotheses were formulated:
 
 
- Null hypothesis (<math>H_0</math>): the score in the healthy lifestyle questionnaire is the same in the intervention and comparison group (or the intervention does not improve the score of the questionnaire).
 
- Alternative hypothesis (<math>H_1</math>): the score in the healthy lifestyle questionnaire is larger for the intervention group than the comparison group.
 
                                 |
| DESIGN                                     | KIS-Antwerp will be implemented and evaluated using a matched cluster-randomized controlled trial involving 6 healthcare centers in Kisantu from where women will be recruited into two study groups: an intervention group and a comparison group.                                                                                                                                                                                                                                                                                                                                                                                                                      |
| STUDY SITE & POPULATION                | The study will take place in 6 healthcare centers across Kisantu, Democratic Republic of Congo (DRC) and will be limited to women of reproductive age (18-49 years) irrespectively of pregnancy status. A total of 144 participants per arm necessary to detect a 12% change in the primary outcome with a level of significance of 0.05, power >80%, and considering a 20% loss of follow-up.                                                                                                                                                                                                                                                                           |
| DURATION                                   | The duration of the present study is 24 months.                                                                                                                                                                                                                                                                                                                                                                                                                                                                                                                                                                                                                          |
| OBJECTIVES AND OUTCOMES                    | This study aims to develop, implement, and evaluate a long-term program (KIS-Antwerp) focused on the prevention of type 2 diabetes mellitus (T2DM) and gestational diabetes (GDM) of women through healthy lifestyle promotion. The primary outcome is a healthy lifestyle score measured by closed-ended questionnaire. Secondary outcomes include anthropometric (weight, body mass index and waist circumference), clinical indicators (blood pressure and glycemia) and other dietary and physical activity questionnaires.                                                                                                                                          |
| INCLUSION & EXCLUSION CRITERIA         | 
To be eligible, study participants must meet the following criteria: Non-pregnant and pregnant (first trimester) women of reproductive age (18-49 years) who have not yet been diagnosed with type 1 diabetes or T2DM.
 
Exclusion criteria entail: Pregnant women with active GDM; Children and adolescents <18 years old; men; women of reproductive age with chronic conditions (e.g. chronic kidney disease); living outside the catchment area of the 6 healthcare centers; women without a permanent home or identified physical address; planning to move elsewhere in the following 2 years; women that do not provide a written informed consent
 |
| SCREENING, RECRUITMENT & RANDOMIZATION | Women of reproductive age (pregnant and non-pregnant) will be recruited primarily through the healthcare centers in Kisantu health district as they attend frequently to healthcare centers due to general consultations. The study is based on a hierarchical design where 2 groups of 3 healthcare centers balanced in population size coverage and geographical location are the units that are randomized to the intervention and comparison group through an algorithm allowing stratified allocation.                                                                                                                                                              |

|                                          |                                                                                                                                                                                                                                                                                                                                                                                                                                                                                                                                                                                                                                                                                                                                                                                 |
|------------------------------------------|---------------------------------------------------------------------------------------------------------------------------------------------------------------------------------------------------------------------------------------------------------------------------------------------------------------------------------------------------------------------------------------------------------------------------------------------------------------------------------------------------------------------------------------------------------------------------------------------------------------------------------------------------------------------------------------------------------------------------------------------------------------------------------|
| STUDY INTERVENTION AND COMPARISON | The intervention group will be provided with a preventive intervention program based on educational + motivational strategies including the following intervention program components: Individualized education, group education, physical activity sessions, setting goals, and usage of a pedometer. The comparison group will be limited to a basic educational strategy only (basic individual education). This design allows us to provide all women with proven effective preventive strategy (education) while testing for the added value of still experimental approaches (motivation).                                                                                                                                                                                |
| FOLLOW-UP                         | Participants will be followed up for 24 months and measurements will be assessed every 6-months period (total of 5-time points: baseline + 4 follow up visits).                                                                                                                                                                                                                                                                                                                                                                                                                                                                                                                                                                                                                 |
| ANALYTICAL METHODS                | Not applicable.                                                                                                                                                                                                                                                                                                                                                                                                                                                                                                                                                                                                                                                                                                                                                                 |
| SAFETY                            | This study imposes a low risk for the participants as the intervention program comprises a lifestyle modification through education and motivational strategies and the measurements to be taken are non-invasive, with the exception of blood glucose assess by blood sampling using a finger prick. For this measurement, guidelines with all the necessary steps and equipment will be followed.                                                                                                                                                                                                                                                                                                                                                                             |
| STATISTICAL METHODS               | Demographic characteristics will be reported as measures of central tendency for continuous outcomes and frequency distribution and percentages for binary/categorical data. Consequently, demographic data will be explored for differences at baseline by comparing and testing means. After the termination of the study, the primary and secondary outcomes will be evaluated for normality by the Kolmogorov-Simonov test and visual inspection of histograms. For the primary ordinal outcome, the impact of the intervention program between baseline and follow up of the 2 groups (intervention and comparison group) will be assessed by using linear mixed models for repeated measurements. The same statistical model will be used to evaluate secondary outcomes. |

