##### **Evaluation study design**

A cluster randomized controlled trial (cRCT) with a hierarchical design will be conducted whereby 2 groups of 3 healthcare centers (in total 6 healthcare centers) will be randomized to an intervention group or comparison group. The intervention group will be provided with the intervention program based on educational + motivational strategies whereas the comparison group will be limited to a basic educational strategy only (**Figure 1**). This design allows us to provide all women with proven effective preventive strategy (education) while testing for a comprehensive approach (education + motivation). The intervention program will last 24 months, starting approximately in September 2021 until September 2023 (Timeline of the study is presented in **Annex 2**).

The intervention program components and topics covered by the intervention group entail the following: Individualized education, group activities (group education and physical activity sessions), goal setting, use of pedometer, and community activities (if possible in the second year of intervention). In contrast, the components compromised in the comparison group are limited to basic individualized education at baseline only. Further information regarding the intervention program components and topics is presented in **Annex 3**.

[figure not shown]

**Figure 1.** Study design and intervention program components

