**Annex 3. Intervention components and topics covered by T2DM and GD preventive intervention program**

| Intervention components                                    | program | Topics                                                                                                                                                                                                                                                                                                             |
|------------------------------------------------------------|---------|--------------------------------------------------------------------------------------------------------------------------------------------------------------------------------------------------------------------------------------------------------------------------------------------------------------------|
| Individualized education (both groups)              |         |                                                                                                                                                                                                                                                                                                                    |
| Dietary advice based on dietary needs of DRC  | -       | Food groups and food sources
Food choices: WHO healthy diet guidelines  considering the Congolese food and cultural profile: dietetic consultation guideline 
Plate distribution; adapted to foods frequently consumed in Kisantu 
A healthy diet during pregnancy |
| Physical activity                                          | -       | WHO physical activity advice and examples 
Physical activity during pregnancy                                                                                                                                                                                                         |
| Educational material                                       | -       | Topics above.                                                                                                                                                                                                                                                                                                      |

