| Group education (intervention group)                |         |                                                                                                                                                                                                                                                                                                                    |
| T2DM and GDM                                  | -       | Definition of T2DM and GDM
Complications
Prevention                                                                                                                                                                                                                                                          |
| Benefits of physical activity                 | -       | Weight control
Prevention of NCDs                                                                                                                                                                                                                                                                               |
| Cooking oils and preparation techniques                    | -       | Cooking methods
Cooking oils
Benefits and risks
Example of healthy cooking methods                                                                                                                                                                                                                        |
| Alcohol and tobacco use                                    | -       | Risks of excessive use                                                                                                                                                                                                                                                                                             |
| Healthy weight gain during pregnancy                       | -       | Benefits and risks
How to reach a healthy weight gain                                                                                                                                                                                                                                                           |

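### The synopsis says the trial tests the added value of motivation, but education also differs between the arms, so the comparison supports a conclusion about the whole programme only

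*Combined protocol and SAP*

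**What the plan says.** The Synopsis entry on study intervention and comparison lists the intervention arm's components as "Individualized education, group education, physical activity sessions, setting goals, and usage of a pedometer". It limits the comparison arm to basic individual education. The same entry then explains that this lets the trial offer education to everyone while "testing for the added value of still experimental approaches (motivation".

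Section 3.1 (Evaluation study design) gives the same rationale with a different ending: "testing for a comprehensive approach (education + motivation". It adds that "The intervention program will last 24 months", and says of the other arm: "In contrast, the components compromised in the comparison group are limited to basic individualized education at baseline only".

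Annex 3 allocates the components. One block is headed "Individualized education (both groups". The next is headed "Group education (intervention group" and covers T2DM and GDM, benefits of physical activity, cooking oils and techniques, alcohol and tobacco, and weight gain in pregnancy. Physical activity classes, goal setting, the pedometer and community activities are also marked for the intervention group only.

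The hypotheses in section 8.1 compare the questionnaire score between the two groups. Section 8.3.3 models the impact of the programme as a whole.

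**The concern.** To attribute a between-arm difference to motivation on top of education, education must be held constant. By the protocol's own labels it is not: one arm gets a second education component that the other does not. It also gets exercise sessions and further organised contact. A positive result could come from any of these or from a mixture.

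What is at stake is the wording of the conclusion. The findings are meant to inform health policy (section 12). A summary that credited motivation would claim something the data cannot show.

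**Working it through.** **1. The plan's own figure, and the contrast it belongs to.** Inputs from sections 4.3 and 8.4: 3 centres per arm, 40 women analysed per centre, difference 6 points, SD 7, ICC 0.1, one-sided 0.05.

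- Design effect = 1 + (40 − 1) × 0.1 = 4.9
- Effective n per arm = 3 × 40 / 4.9 = 24.49
- Standard error = 7 × √(2 / 24.49) = 2.00
- Power = Φ(6 / 2.00 − 1.645) = Φ(1.355) = 0.91

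This reproduces the stated 91%. It is power for the difference between the whole package and basic baseline education. The documents give no effect size, arm or power for motivation alone.

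**2. The arms side by side** (Synopsis, sections 3.1, 5.1 and 5.3, Annex 3).

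| Element | Intervention | Comparison |
|---|---|---|
| Individual education | Yes | Basic, baseline only |
| Group education, five topics | Yes | No |
| Physical activity classes | Yes | No |
| Goal setting | Yes | No |
| Pedometer | Yes | No |
| Community activities, year 2 | If acceptable | No |
| Focus groups every 6 months | Yes | No |
| Measurement visits | 5 time points | 5 time points |

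**3. Does the answer depend on what counts as motivation?** The documents do not define it, so take two readings.

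- Broad: everything not labelled education is motivational. The contrast is then motivation plus group education.
- Narrow: only goal setting and the pedometer are motivational. The contrast is then motivation plus group education, exercise sessions and any community activities.

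Under neither reading is motivation the only difference. Group education is labelled education and sits in one arm under both.

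**4. Identification.** Write the between-arm difference as D = E + X + C + M, for extra education, exercise sessions, extra contact and motivation (interactions ignored). The trial estimates D: one equation, four unknowns. Even if every term is taken as non-negative, any M from 0 to D fits the same result. Sections 8.3.3 to 8.3.6 plan no component or mediation analysis that would narrow this.

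**5. Could the other parts matter on the scale used?** In Annex 6, Q13 (exercise days) and Q14 (session length) each score 1 to 5. Together they can move one woman's score by (5 − 1) + (5 − 1) = 8 points, against a target mean difference of 6. Class frequency and length are not stated, so the following is an assumption. Take a woman who first answers never and under 10 minutes, and who then attends one or two classes a week. Q13 goes from 1 to 2 (+1). Q14 goes from 1 to 3 if classes last 20–30 minutes (+2), or to 5 if over 40 minutes (+4). The total is +3 to +5. This is one woman starting at the bottom of both items, not a group mean, and it bears on the issue only under the narrow reading in step 3.

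**The case against.** The strongest reply is that this is one loose clause in a rationale. The surrounding text is right: the same synopsis entry lists group education for one arm only, section 3.1 speaks of a comprehensive approach, and section 11.5 contrasts a comprehensive strategy with a basic one. The clause says that all women receive education, not that they receive equal education. Comparing a package with basic education is a legitimate pragmatic design. All of this stands, and it keeps the point small. It does not rescue the clause, because a claim about the added value of motivation still needs equal education.

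The reply also defeats several stronger readings that a reader might infer.

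- *That motivation is the trial's stated question, or that the design fails.* The objectives, hypotheses and primary analysis all concern the programme, and the two arms can answer that.
- *That the contrast is 24 months of contact against a single session.* Section 3.1 gives a programme duration and a baseline-only restriction. No number, frequency or length of sessions appears, and the scheduled measurement visits are the same in both arms.
- *That the comparison arm hears nothing on the group topics.* The shared individual education in Annex 3 covers physical activity, including in pregnancy, and diet in pregnancy, so the subject areas partly overlap.
- *That integration into the health system would be misdirected.* Section 2 offers the programme as a whole for integration, which is what the trial compares.

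**Conclusion.** The synopsis clause is wrong as written, and the two-arm comparison is not. The trial can support a conclusion about the multicomponent programme against basic individual education at baseline. It cannot support one about motivation added to education.

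The size is five listed components against one, with a possible sixth in year 2. At least one of the unshared components is education by the protocol's own label. The share of any effect due to motivation is not identifiable, and the extra contact is real in kind but cannot be quantified. No estimate, power figure or procedure is affected. The conclusion rests on the labels in Annex 3 and the baseline-only restriction in section 3.1, and it does not depend on how motivation is defined.

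**What to change.** Replace the synopsis clause with wording such as:

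> The trial tests the whole multicomponent programme (individual and group education, physical activity sessions, goal setting, pedometer, and community activities if adopted) against basic individual education at baseline only. It does not separate motivation from additional education, exercise sessions or contact.

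Hold the report's conclusion to the package in the same terms. Section 3.1 already frames the aim suitably and needs at most the second sentence added. The cost is wording only: the sponsor gives up a claim about motivation alone, and sample size and analysis stay as planned.
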